### Dose and administration

Ixekizumab/placebo will be administered by the participant via subcutaneous (sc.) injections for a total treatment period of 12 months. Two sc. injections (160 mg) will be administered at week 0, one dose (80 mg) at week 2, 4, 6, 8, 10 and 12 and continue with a maintenance dose (80 mg) every fourth week for a total treatment period of 12 months. The same dosing schedule is used for treatment of psoriasis.

The syringes for ixekizumab and placebo will have a similar look and not be possible to distinguish. Each syringe will contain 1 mL solution of ixekizumab or placebo. The syringes containing ixekizumab will deliver 80 mg of ixekizumab.

Ixekizumab and placebo will be provided by Eli Lilly and Company through their investigator-initiated trials program.

### Concomitant medication

Concomitant medications and other treatments known to influence glucose levels prescribed before study entry will, if possible, remain unchanged during the study period unless changes are made for safety reasons. This includes types of insulins, as well as glucose sensors and types of insulin delivery (injections/insulin pump). Concomitant medication will be recorded in the electronic Case Report Form (eCRF) at every clinical visit.

### Adherence to treatment

Compliance and adherence to protocol and treatment will be checked at each contact with the participant. The unused amount of trial product will be assessed against the dispensed amount, and, in case of discrepancies, the participant must be asked about compliance.

### Continuous glucose monitoring

Masked CGM will be performed during 14 days at each of the following time points: run-in period, week 13, week 26 and week 52. At week 52, masked CGM will be set at some time point during the 4 weeks preceding the 52 week visit since masked CGM needs to be collected during treatment with ixekizumab/placebo. The participant’s own CGM use for their conventional treatment should be continued and changes will be determined by regular clinical diabetes care.

### Study visits

The visit schedule will be as follows: randomisation, week 2, 4, 13, 26, 39 and 52. MMTT will be performed at randomisation, week 4, 26 and 52. At all visits, physical examinations will be performed and HbA1c collected. Blood pressure and weight will be taken at all visits except week 2. A detailed description of the trial procedures is provided in table 2. Additionally, participants will complete a series of questionnaires evaluating intervention treatment satisfaction, well-being, hypoglycaemia confidence, diabetes-related distress and physical activity at the study site:

Diabetes Treatment Satisfaction Questionnaire (DTSQ) is an 8-item scale measuring aspects of satisfaction scored on a 7-point Likert scale, including domains of current treatment satisfaction, convenience of treatment, understanding of diabetes, recommendation of treatment and continuation of treatment. Two versions will be used: the DTSQs and DTSQc. DTSQs is used to record current treatment satisfaction throughout the trial and the DTSQc is used to retrospectively compare the treatment arms at week 52.^16^

**Table 2 T2:** Trial procedures

	Patient info (two visits)	Screening visit (fasting*)	Baseline randomisation (fasting)	Week 2 Follow-up±1 week	Week 4 Follow-up±10 days (fasting)	Week 13 Follow-up±2 weeks	Week 26 Follow-up±2 weeks (fasting)	Week 39 Follow-up±2 weeks	Week 52 Follow-up±2 weeks (fasting)		Weeks 104 and 208 Extension phase (±3 months) (fasting)	
Variables	Visit 1	Visit 2	Visit 3	Visit 4	Visit 5	Visit 6	Visit 7	Visit 8	Visit 9		Visit 10+11	
Information visit	X											
Obtain informed consent	X											
Inclusion/exclusion criteria		X										
ECG		X										
Demographics		X										
Length		X										
Medical history		X	X						X			
Date of diagnosis of type 1 diabetes and first insulin injection		X										
Smoking status			X									
Family history of type 1 diabetes		X										
Concomitant medication		X	X	X	X	X	X	X	X			
Physical examination		X	X	X	X	X	X	X	X			
Blood pressure			X		X	X	X	X	X			
Weight		X	X		X	X	X	X	X			
Information regarding type of glucose monitoring			X			X	X	X	X		X	
GAD, ZnT8, insulin/IAA and IA-2-antibodies		X							X			
Mixed Meal Tolerance Test		X	X		X		X		X		X	
HbA1c		X	X		X	X	X	X	X		X	
Proinsulin			X						X			
Hematology†		X	X		X		X		X			
Clinical Chemistry‡		X	X		X		X		X			
Urine pregnancy test		X										
HIV, hepatitis serology, IgA transglutaminase, thyroid status		X										
Tuberculosis screening (QuantiFERON and chest X-ray)		X										
Liver status§		X	X		X		X		X			
Downloading CGM data from Libre Pro iQ		*	X			X	X		**	X	***	X (2 visits)
Sampling for biobank			X		X		X		X			
Types of insulin and doses of insulin			X		X		X		X		X	
Questionnaries¶			X				X		X			
Adverse events			X	X	X	X	X	X	X			

*During this visit, Libre Pro iQ will be initiated to collect masked CGM data.

**CGM will be initiated 4 weeks preceding this visit and the data collected at week 52.

***CGM will be initiated at week 104 and 208 and the data will be collected at a separate visit.

* Blood samples will be taken in a fasting state.

† Hb, MCV, WBC, platelets, absolute counts of neutrophils (segmented), lymphocytes, monocytes, eosinophils, basophils.

‡ Na, K, Ca, CRP, Creatinine.

§ 3AST, ALT, Alkaline phosphatase, Bilirubin (total and direct).

¶ DTSQs, WHO-5, SWE-HCS, SWE-PAID-20 and IPAQ (at Week 52, DTSQc is included).

World Health Organization-5 (WHO-5) is a 5-item scale that assesses patient well-being.^17^The hypoglycaemia confidence questionnaire is a 9-item scale that evaluates patient confidence regarding their ability to prevent and address hypoglycaemic events.^18^Problem Areas in Diabetes Scale, Swedish version (SWE-PAID) is a 20-item scale which assesses worries and concerns specifically related to diabetes and its management. It has been shown to be a good marker of diabetes-related distress.^19^International Physical Activity Questionnaire (IPAQ) is a 7-item scale that assesses minutes spent in light, moderate and vigorous physical activity per week. Scores are expressed as energy expenditure in estimated metabolic equivalent task minutes.^20^

### Mixed meal tolerance test

The golden standard for evaluating endogenous insulin production is a 2-hour MMTT.^21^ The participants will consume a standard liquid meal (Fresubin) after an overnight fast >10 hours before the test. The liquid consists of fat, carbohydrates and protein based on body weight. P-glucose and c-peptide will be measured with seven sampling time points (−10, 0, 15, 30, 60, 90 and 120 min) after consuming the liquid. For details, see the procedure in the online supplemental material.

### Dropouts

Participants who drop out from the study will be asked for a follow-up on an additional visit and the following blood samples will be checked: HbA1c, C-peptide and proinsulin. Insulin doses and concomitant medications will be recorded. The dropouts will not be replaced.

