### Endpoints

The primary endpoint will be the change in residual insulin secretion measured by stimulated C-peptide 2-hour area under the curve profile measured by MMTT between baseline and week 52. The secondary endpoints are insulin need (U/kg), time in glucose range (3.9–10 mmol/L), time in hypoglycaemia (<3.9 mmol/L) and HbA1c. Exploratory variables include glycaemic variability, well-being, hypoglycaemia confidence, treatment satisfaction and diabetes-related distress. All predefined endpoints are shown in box 1.

Box 1Predefined endpointsPrimary endpointChange in residual insulin secretion measured by stimulated C-peptide 2 hour area under the curve profile measured by mixed meal tolerance test (MMTT) between baseline and week 52.Secondary endpointsChange in mean Insulin dosage per kilo body weight for 24 hours from baseline to week 52.Change in time with glucose levels in range (3.9-10 mmol/l) measured by masked CGM (Libre Pro iQ) from baseline to week 52.Change in time with hypoglycaemia (<3.9 mmol/l) measured by masked CGM (Libre Pro iQ) from baseline to week 52.Difference in HbA1c from baseline to week 52.Exploratory endpointsChange in time in hypoglycaemia (<3.0 mmol/l) measured by masked CGM (Libre Pro iQ) from baseline to week 52.Change in proinsulin/c-peptide ratio in serum as a measure of beta cell stress from baseline to week 52.Change in time in target (3.9-8 mmol/l) measured by masked CGM (Libre Pro iQ) from baseline to week 52.Change in time in hyperglycaemia >10 mmol/l and >13.9 mmol/l measured by masked CGM (Libre Pro iQ) from baseline to week 52.Change in glycaemic variability measured by SD, CV and MAGE by masked CGM (Libre Pro iQ) from baseline to week 52.Change in proportion of patients with peak residual insulin secretion measured by MMTT: stimulated C-peptide >0.4 nmol/mL from baseline to week 52.Change in WHO-5 scores from baseline to week 52.Change in DTSQs scores from baseline to week 52.Change in DTSQc scores estimated at week 52.Change in HCS scores from baseline to week 52.Change in PAID scores from baseline to week 52.Change in IPAQ scores from baseline to week 52.The same variables described above regarding primary, secondary and exploratory endpoints will be evaluated if the variable is measured at a specific time point from baseline to week 4, baseline to week 13 as well as baseline to week 26.

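### The assessments listed for the dropout visit do not yield the primary endpoint, because no MMTT is named and the visit is not tied to week 52

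*Protocol article*

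**What the plan says.** **Dropout rule (Dropouts).** Participants who drop out are to be "asked for a follow-up on an additional visit and the following blood samples will be checked: HbA1c, C-peptide and proinsulin". The section adds: "Insulin doses and concomitant medications will be recorded". It gives no time for the visit and does not mention an MMTT. It closes with: "The dropouts will not be replaced".

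**Primary endpoint (Endpoints and Box 1).** This is the "change in residual insulin secretion measured by stimulated C-peptide 2-hour area under the curve profile measured by MMTT between baseline and week 52".

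**What the AUC needs (Mixed meal tolerance test).** After an overnight fast and a standard liquid meal, "P-glucose and c-peptide will be measured with seven sampling time points (−10, 0, 15, 30, 60, 90 and 120 min".

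**Schedule (Study visits, Table 2).** MMTTs during treatment are planned at randomisation and weeks 4, 26 and 52. The week-52 visit has a window of ±2 weeks.

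**Analysis (Statistical analysis).** The full analysis set takes in everyone dosed who has at least one follow-up measurement, without saying of which variable. The primary analysis is an ANCOVA of the change to week 52, adjusted for baseline AUC.

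**The concern.** The endpoint is a stimulated, timed profile at a fixed week. The dropout rule lists a C-peptide sample at whatever time the extra visit takes place. A single C-peptide value cannot be turned into a 2-hour AUC, and a value taken at an arbitrary time is not a week-52 value. A site that does exactly what the section lists will finish the visit without the primary outcome.

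What is at stake is bias. If leaving is related to adverse effects or to a perceived lack of benefit, those with an observed week-52 AUC are no longer the randomised groups. No AUC collected after departure would be available to test an assumption about those who left. An analysis plan can choose how to handle a missing AUC, but it cannot recover one that was never measured.

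**Working it through.** **1. The plan's own numbers.** Inputs from Sample size calculation: difference 0.18 nmol/L, SD 0.34 nmol/L, two-sided alpha 0.05, power 80%, dropout 10%. Allocation of 1:1 is my assumption; the article does not state the ratio.

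- Per arm, normal approximation: n = 2 × (1.960 + 0.842)² × (0.34/0.18)², just over 56, rounded up to 57. The exact t-test solution is 56.98, also 57. Total 2 × 57 = 114, as stated. Power at 57 per arm is 0.800 (t-test).
- Inflation: 114 / (1 − 0.10) = 126.7, rounded up to 127, as stated.

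**2. How many lack the outcome.** 127 × 0.10 = 12.7, about 13. That leaves about 114 with a week-52 AUC, the number the calculation requires.

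**3. Power if dropouts contribute no primary value** (0.18 nmol/L, SD 0.34, 127 randomised; every rate other than 10% is an assumption):

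| Dropout | Power (t-test) |
|---|---|
| 0% | 0.841 |
| 5% | 0.822 |
| 10% (plan) | 0.801 |
| 15% | 0.778 |
| 20% | 0.753 |

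At the planned rate nothing is lost against the stated target.

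**4. Endpoint against dropout visit.**

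| Needed for the primary endpoint | Listed for the dropout visit |
|---|---|
| MMTT after an overnight fast | Not named |
| Seven timed C-peptide samples over 2 hours | C-peptide sample; number and timing not given |
| Week 52 (±2 weeks) | One extra visit, no time given |

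None of the three requirements is met by what is listed. The timing is a separate obstacle: even an MMTT at that visit would give a week-52 value only if the visit fell at week 52.

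**5. What dropouts may still have.** Someone leaving before week 4 has no post-baseline AUC. Someone leaving between weeks 4 and 26 can have one, and someone leaving after week 26 can have two. Any of them with some follow-up measurement can belong to the full analysis set while having no observed outcome for the week-52 ANCOVA.

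**The case against.** **The C-peptide sample may be an MMTT.** A reader might infer that the plan replaces the MMTT with a single unstimulated sample, so that the outcome is missing by design. The article does not say this. Lab, monitoring and study drug delivery counts C-peptide taken during the MMTT among the blood samples. Table 2 has no separate C-peptide row, and Sample size calculation uses the bare term for the stimulated measure. Against that, the article elsewhere names the MMTT when it describes the test, and C-peptide beside proinsulin also fits the exploratory ratio in Box 1. The intention is open. What stands is that the listed items do not yield the endpoint and that the visit has no date.

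**Only completers can be analysed.** A reader might infer this too, but it goes too far. Weeks 4 and 26 supply AUCs for some dropouts, and the handling of missing data may sit in an analysis plan that is not shown. Using those AUCs still rests on an assumption about the course after departure, which the listed samples cannot check.

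**Stopping drug is not leaving the study.** The section concerns people who leave the study. Nothing in the article says that a participant who only stops injections loses the week-52 MMTT, so the point does not extend to them.

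**A figure for the bias.** One could assume that ixekizumab dropouts decline like placebo and scale a completer effect of 0.18 to 0.9 × 0.18 = 0.162, or at an assumed 20% dropout to 0.8 × 0.18 = 0.144. The apparent overstatements of 11% and 25% merely restate 1/(1 − d), where d is the dropout proportion. They are not estimates from this trial.

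**The rest of the rule.** The visit has value as it is: HbA1c and insulin dose are secondary variables. Not replacing dropouts is no defect, since the sample size allows for them.

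**Conclusion.** The point holds in a limited form. Followed as written, the dropout rule does not supply the week-52 2-hour MMTT C-peptide AUC. About 13 of 127 participants would be affected if dropout is the planned 10%. The sample size of 114, inflated to 127, reproduces, and power at that rate is about 0.80, so this is neither an error in N nor a loss of planned power. The consequence is a risk of bias from unobserved week-52 outcomes. Its direction and size depend on who leaves and why, and the document gives no basis for estimating either.

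The conclusion rests on reading the Dropouts section as a full list of what is collected at that visit. The full protocol and the online supplement are not shown. If an MMTT at week 52 is already intended, the section needs only to say so.

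**What to change.** Amend the Dropouts section so that participants who leave early and agree to a further visit are asked to attend for the scheduled week-52 MMTT. If they accept only another date, perform an MMTT as near week 52 as possible and record the date. State that this attendance does not count as the re-entry barred under Randomisation.

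Include week-52 values obtained in this way in the full-analysis-set primary ANCOVA. A value dated outside the ±2-week window should not be labelled week 52, and its use should be specified before unblinding.

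The cost is a small amendment and a longer visit for a few people, some of whom will decline. The week-52 MMTT is already scheduled for every participant, so no new procedure is introduced. The benefit is limited by timing. Inclusion began in September 2022, the last randomisation was anticipated in May 2025, and the article appeared in November 2025. On that timetable the latest entrants reach week 52 around May 2026, and anyone randomised before about November 2024 had already passed it at publication. The change can help only participants who have not yet passed week 52, so it will reach fewer than the full 13. For the others, the report should state how many dropouts have no week-52 AUC in each arm.

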### Post-study treatment

There will be no difference from the expected normal treatment of type 1 diabetes after the participants have ended the participation in the trial.

### Endpoints

The primary endpoint will be the change in residual insulin secretion measured by stimulated C-peptide 2-hour area under the curve profile measured by MMTT between baseline and week 52. The secondary endpoints are insulin need (U/kg), time in glucose range (3.9–10 mmol/L), time in hypoglycaemia (<3.9 mmol/L) and HbA1c. Exploratory variables include glycaemic variability, well-being, hypoglycaemia confidence, treatment satisfaction and diabetes-related distress. All predefined endpoints are shown in box 1.

Box 1Predefined endpointsPrimary endpointChange in residual insulin secretion measured by stimulated C-peptide 2 hour area under the curve profile measured by mixed meal tolerance test (MMTT) between baseline and week 52.Secondary endpointsChange in mean Insulin dosage per kilo body weight for 24 hours from baseline to week 52.Change in time with glucose levels in range (3.9-10 mmol/l) measured by masked CGM (Libre Pro iQ) from baseline to week 52.Change in time with hypoglycaemia (<3.9 mmol/l) measured by masked CGM (Libre Pro iQ) from baseline to week 52.Difference in HbA1c from baseline to week 52.Exploratory endpointsChange in time in hypoglycaemia (<3.0 mmol/l) measured by masked CGM (Libre Pro iQ) from baseline to week 52.Change in proinsulin/c-peptide ratio in serum as a measure of beta cell stress from baseline to week 52.Change in time in target (3.9-8 mmol/l) measured by masked CGM (Libre Pro iQ) from baseline to week 52.Change in time in hyperglycaemia >10 mmol/l and >13.9 mmol/l measured by masked CGM (Libre Pro iQ) from baseline to week 52.Change in glycaemic variability measured by SD, CV and MAGE by masked CGM (Libre Pro iQ) from baseline to week 52.Change in proportion of patients with peak residual insulin secretion measured by MMTT: stimulated C-peptide >0.4 nmol/mL from baseline to week 52.Change in WHO-5 scores from baseline to week 52.Change in DTSQs scores from baseline to week 52.Change in DTSQc scores estimated at week 52.Change in HCS scores from baseline to week 52.Change in PAID scores from baseline to week 52.Change in IPAQ scores from baseline to week 52.The same variables described above regarding primary, secondary and exploratory endpoints will be evaluated if the variable is measured at a specific time point from baseline to week 4, baseline to week 13 as well as baseline to week 26.

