### Screening

Individuals with type 1 diabetes are monitored at their own clinic and receive verbal or written information about the study during a visit at the hospital, or written information via mail and verbal information via telephone. If individuals are interested in participating, verbal and written informed consent will be obtained from each individual by an investigator (physician) at the study site. During the screening visit, inclusion and exclusion criteria will be examined. Major inclusion criteria are diagnosis of type 1 diabetes and first injection of insulin within 100 days prior to screening, age 18–45 years old, presence of at least one of the autoantibodies (insulin/IAA, GAD-65, ZnT8 or IA-2) at clinical practice or at screening and have a remaining stimulated peak C-peptide >0.20 nmol/L during a mixed meal tolerance test (MMTT). For all inclusion and exclusion criteria, see table 1.

**Table 1 T1:** Inclusion and exclusion criteria

Inclusion criteria	Exclusion criteria

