Subjects eligible for inclusion in the study have to fulfil all of the following criteria: Signed informed consent and expected cooperation of the patients for the treatment and follow-up must be obtained and documented according to ICH GCP, and national/local regulations before trial activities are begun. Must be willing and capable of taking the study drugs and meet for tests and follow-up as described. Diagnosed type 1 diabetes (E10.9) within 100 days. First injection of insulin maximum 100 days prior to screening. If aged 36–45 years, a current insulin regimen of both basal and prandial insulin or alternatively use of an insulin pump should exist. Aged 18–45 years old. Presence of antibodies at clinical practice or at screening to at least one of the following antigens: insulin/IAA, GAD-65, IA-2 and ZnT8. Remaining stimulated peak C–peptide ≥0.20 nmol/L. If age 36–45 years, peak C-peptide should be <2.0 nmol/L. Effective contraceptive methods throughout the study.	Subjects fulfilling any of the following criteria are not eligible for inclusion in this study: Contraindications to ixekizumab. Treatment with any oral or injected glucose-lowering agents other than insulin. A history of haemolytic anaemia or significantly abnormal haematology/coagulation results at screening. Participation in other clinical trials with a new chemical entity within the previous 3 months. Subjects with severe obesity (BMI >35 kg/m^2^ if age 18–35 years and BMI >30 kg/m^2^ if age 36–45 years). Subjects with other autoimmune diseases, for example, Mb Crohn, Ulcerative colitis, Graves' disease, psoriasis, psoriatic arthritis and axial spondylarthritis, except coeliac disease and hypothyroidism, which do not need to be excluded. Active serious or chronic infections (ie, in case the patient had a serious infection (eg, pneumonia, cellulitis), has been hospitalised, has received intravenous antibiotics for an infection within 12 weeks prior to screening visit, had a serious bone or joint infection within 24 weeks before screening visit, has ever had an infection of an artificial joint. Known immunodeficiency or patient is immunocompromised to an extent that participation in the study would pose an unacceptable risk to the patient. Active or latent tuberculosis. HIV or active hepatitis B or C. Active or recurrent fungal infection. Subjects with myocardial infarction, stroke, unstable angina or heart failure in the last 6 months. Current clinically significant cardiac arrhythmias as verified by ECG. Planned surgery during the treatment period of the study (except minor surgery on skin lesions, eg, nevus). For female subjects: Positive pregnancy test, presently breast-feeding or unwillingness to use effective contraceptive measures for the duration of the study and 3 months after discontinuation. For male subjects: intent to procreate during the duration of the study or within 3 months after discontinuation or unwillingness of their partner to use effective contraceptive measures for the duration of the study and 4 months after discontinuation. Any history of malignancy in the last 5 years except for completely resected squamous or basal cell carcinoma of the skin. Administration of live attenuated vaccine(s) (LAV) within 2 months of enrolment. Or intended use of LAV during the treatment period. The investigator judges that the clinical diagnosis of type 1 diabetes set is incorrect or uncertain (needs to be confirmed by discussion with experienced diabetologist if excluding due to this criterion) Allergy against ingredients of the investigational products. Known allergy or hypersensitivity to any biologic therapy (active substance or excipients) that would pose an unacceptable risk to the patient if participating in the study. Presence of serious disease or condition, which in the opinion of the investigator makes the patient non-eligible for the study. Liver injury criteria: patients with active hepatobiliary diseases or at screening having alanine aminotransferase (ALT) or aspartate aminotransferase (AST) >2.5 times the upper limit of normal (>2.5 x ULN). Laboratory abnormalities at screening: Neutrophil count <1500 cells/μL (=1,5 *10^9^ cells/ L) Platelet count <100 000 cells/μL (= 100 *10^9^ cells/ L) Haemoglobin <8.5 g/dL (= <85 g/L) (males) and <8 g/dL (= <80 g/L) (women)

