### Sample size calculation

In a previous study of 191 individuals with type 1 diabetes followed from diagnosis and year onwards, stimulated c-peptide decreased from 0.70 to 0.46 nmol/L.^6^ The observed SD for c-peptide was 0.34 nmol/L. In two other studies, the SD has been suggested to be 0.25 nmol/L.^22 23^

Using an SD of 0.34 nmol/L, our power calculations indicate that 114 participants would be needed to detect a 25% reduction in c-peptide decline (0.18 nmol/L difference), with two-sided t-test with a power of >80% and significance level of 0.05. If the SD is 0.25 nmol/L, we will also have power to detect a treatment difference of 0.14 nmol/L. We have, therefore, planned to include 114 participants, with an assumed dropout rate of 10%, 127 participants are required.

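### The exploratory C-peptide threshold endpoint in Box 1 is set in nmol/mL, which puts the cut-off at 400 nmol/L, far outside the range the rest of the protocol implies

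*Protocol article*

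**What the plan says.** In the protocol article, Endpoints, Box 1, one of the exploratory endpoints is described as "Change in proportion of patients with peak residual insulin secretion measured by MMTT", with the threshold given as "stimulated C-peptide >0.4 nmol/mL from baseline to week 52". The closing sentence of Box 1 extends the listed endpoints to weeks 4, 13 and 26 wherever the variable is measured. The Study visits section places mixed meal tests at randomisation and weeks 4, 26 and 52. The Statistical analysis section assigns dichotomous variables to Fisher's exact test.

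Elsewhere C-peptide is always in nmol/L:

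- Screening, for entry to the trial: "remaining stimulated peak C-peptide >0.20 nmol/L during a mixed meal tolerance test".
- Table 1, for the older age band: "If age 36–45 years, peak C-peptide should be <2.0 nmol/L".
- Sample size calculation, for the expected course over the first year: "stimulated c-peptide decreased from 0.70 to 0.46 nmol/L".
- Sample size calculation, for the spread: "The observed SD for c-peptide was 0.34 nmol/L", and from two other studies "the SD has been suggested to be 0.25 nmol/L".

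Nothing in the article explains or corrects the different unit in Box 1.

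**The concern.** The two eligibility limits and the Box 1 cut-off concern the same measurement, peak stimulated C-peptide in a mixed meal test, yet the units differ by a factor of 1,000. A threshold is the whole definition of an endpoint of this kind. If it lies beyond any value the trial can produce, the endpoint cannot vary.

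Two things are at stake. If the printed definition were carried into the analysis, the comparison would be empty at weeks 4, 26 and 52. If the analysis instead uses nmol/L without a recorded correction, the reported endpoint will differ by a factor of 1,000 from one published under the title of predefined endpoints, and a reader comparing the two cannot tell a unit slip from a changed threshold.

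**Working it through.** **1. Convert the cut-off.** 0.4 nmol/mL × 1,000 mL/L = 400 nmol/L.

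**2. Compare it with the article's other C-peptide values.**

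| Value | Source | 400 nmol/L divided by it |
|---|---|---|
| 0.20 nmol/L, floor for peak | Screening; Table 1 | 2,000 |
| 2.0 nmol/L, ceiling for peak, ages 36–45 | Table 1 | 200 |
| 0.70 nmol/L, mean at diagnosis | Sample size calculation | about 571 |
| 0.46 nmol/L, mean one year on | Sample size calculation | about 870 |

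**3. Confirm that nmol/L is the trial's working scale.** Take a difference of 0.18 nmol/L, SD 0.34 nmol/L, two-sided alpha 0.05 and 80% power, and assume equal allocation. The usual two-sample formula gives 57 per arm, so 114 in total (power 80.7% by the normal approximation, 80.0% by the t-test). Then 114 / 0.9 = 126.7, rounded up to 127. The article's own sample size is reproduced in nmol/L.

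**4. Share of patients above the cut-off as printed.** The planning means and SDs serve here as a stand-in for peak values, because the article does not say that they are peaks.

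- Normal scale, mean 0.70: (400 − 0.70) / 0.34 = 1,174 SDs above the mean; with SD 0.25, 1,597.
- Normal scale, mean 0.46: (400 − 0.46) / 0.34 = 1,175; with SD 0.25, 1,598.
- Lognormal scale with the same means and SDs: 10.6 to 18.5 log-SDs above.

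The probability of exceeding the cut-off is effectively zero in every case. With no patient above it in either arm, Fisher's exact test returns p = 1.

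**5. Share above the cut-off if the unit is nmol/L.** P(C-peptide > 0.4 nmol/L), same stand-in values:

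| Mean | SD | Normal | Lognormal |
|---|---|---|---|
| 0.70 | 0.34 | 81% | 84% |
| 0.70 | 0.25 | 88% | 93% |
| 0.46 | 0.34 | 57% | 45% |
| 0.46 | 0.25 | 59% | 51% |

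On that reading the proportion is neither 0% nor 100% and can move over the year, which supports nmol/L as the intended unit.

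**6. How sharp would the corrected endpoint be?** Take a one-year mean of 0.46 against 0.46 + 0.18 = 0.64 nmol/L, normal distributions and an assumed 57 per arm.

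- SD 0.34: 57% against 76% above 0.4 nmol/L; exact power of Fisher's test about 50%.
- SD 0.25: 59% against 83%; power about 76%.

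For comparison, the t-test on the continuous value has 80% power at SD 0.34 (step 3).

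**The case against.** The strongest reply is that this is a typographical slip in one of many exploratory endpoints in a journal article. The abstract does not mention the endpoint, and the running text of the Endpoints section does not name it among its exploratory examples. C-peptide is measured at a central laboratory and every other value is in nmol/L, so a literal 400 nmol/L cut-off would probably be noticed at the first tabulation. The full protocol, the analysis plan and the derivation specification are not shown and may already have the right unit. All of this stands and limits the severity. It does not remove the point, because the published definition is still wrong as written.

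Four stronger readings are tempting, and the documents do not support them:

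- **That the trial's main C-peptide analysis is compromised.** The primary endpoint is an area under the curve with no threshold, and the sample size is reproduced in nmol/L.
- **That 0 of 127 participants would exceed the cut-off at week 52.** The plan itself allows for 10% dropout without replacement, so about 114 would be evaluable. The supportable statement is a proportion of effectively 0%.
- **That the endpoint discriminates well once corrected.** At the SD used to size the trial its power is only about 50% on the stand-in values in step 6.
- **That the unit error calls for a different test.** Fisher's exact test between randomised arms at week 52 is valid. Baseline adjustment is a separate question of efficiency.

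**Conclusion.** The point holds as a minor correction: the Box 1 cut-off is wrong as written. At 400 nmol/L it is 200 to 2,000 times the eligibility limits for the same peak measurement, and it would give effectively 0% in both arms at every mixed meal test. The effect is confined to this exploratory endpoint; the primary and secondary endpoints and the sample size are untouched.

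The conversion and the conflict with the other units need no assumption. The 0% figure rests on two things. Participants aged 18–35 have no stated upper C-peptide limit, so for them it depends on the planning means and SDs rather than on an eligibility ceiling. Those means are also not identified as peak values. Peaks may run higher than the means, but a gap of several hundred-fold leaves no realistic doubt. That the intended cut-off is 0.4 nmol/L is a strong inference from the rest of the article, not something it states, and whether the error reaches the analysis plan or the programming cannot be judged from what is shown.

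**What to change.** The sponsor should confirm the intended unit, evidently nmol/L, and correct the cut-off in Box 1 with a dated correction before unblinding. The same check should cover the statistical analysis plan and the derived-variable specification, with a change there only if they repeat nmol/mL. The cost is one unit in the text and a short check of two documents; no data collection, sample size or analysis method changes.

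Separately and optionally, the week-52 comparison of this proportion could be adjusted for baseline peak C-peptide, which is already collected at the randomisation visit. That would be a change of analysis method, to be decided on its own merits before unblinding; the unit correction does not depend on it.
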